### Randomization and blinding

Participants will be allocated to groups (intervention or control group) randomly in 1:1 rate. The randomization sequence will be generated by an independent professional using an online system (www.randomization.com) to allocate 22 participants from each frailty group (i.e. frail, pre-frail and robust) to the control group (*n* = 66) and in the intervention group (*n* = 66). The type of intervention that the participant will undergo during the study will be indicated on a sheet of paper inserted in opaque, sequentially numbered, sealed envelopes. These envelopes will be prepared by a researcher who is not involved in enrolling the participants, in assigning them to their groups or performing follow-up measurements and will be delivered after baseline measurement. Follow-up measurement at the end of intervention period and after 3 months will be performed by a researcher who will be unaware of group allocation.

The professionals responsible for the physical and blood assessments will be blind to participant’s group. It will not be possible to blind the allocation of groups from the professional responsible for the intervention since the VIVIFRAIL protocol change according to patients’ profile. It will not be possible to hide the intervention of the participants, who will know about the allocation in different groups at random. However, they will not be aware of which group they were allocated. Raters and data-analysts will keep blinded in relation to the intervention performed by the volunteer.

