- Fatigue: it will be evaluated through self-report using questions 7 and 20 of the Center for Epidemiological Studies - Depression (CES-D) scale. The volunteers will be asked about the frequency in which they perceived to make an effort to perform usual tasks and the frequency with which they were unable to carry out their activities in the last week. Positive affirmation “most of the time” or “always” in any of the two questions will be considered a manifestation of fatigue.

- Unintentional weight loss in the last year: older person with unintentional weight loss greater than 5% of body weight will be scored according to this criterion, adjusted for sex and body mass index (BMI).

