### Interventions

#### Control group

To ensure that possible changes in the serum levels of biomarkers were not related to frailty, participants allocated to control group will participate in monthly meetings of health promotion. To minimize bias effect of socialization on the perception of health, the meetings will include lectures on topics related to health, such as food, use of medicines, prevention and health promotion and socialization activities [29]. Participants will be guided to continue the usual primary and secondary health care (public or private) and community activities. Telephone contact will be made after absences from meetings.

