#### Intervention group

The VIVIFRAIL© [15, 19] multicomponent exercise intervention protocol was developed in Europe (Erasmus+programme, European Union) and consists of resistance training, gait retraining, and balance training. Different functional capacity levels will be determined based on the scores obtained from the SPPB and the 6-m gait velocity test, with each leading to the recommendation of a certain customized multicomponent physical exercise program (Program A, B, C1, C2 or D). These programs are composed by arm and leg strength and power exercises, balance and coordination to prevent falls, flexibility and cardiovascular endurance exercises [15, 19].

After the initial assessment and categorization of the volunteer in any of the physical exercise programs, a multicomponent program will be carried out for 12 weeks, totaling 60 sessions. Two weekly supervision sessions will be held, lasting 60 min each, with an interval of 1 day between them. Participants will receive the materials (elastic bands, towel and bottles with water/sandy) to perform the exercises and will be trained to perform exercises individually at home with a frequency of 3 days a week, in order to complete 5 days of activity per week. Instructions will be properly adapted to the focused population and will be provided to the volunteers in the Portuguese language.

The VIVIFRAIL© program is composed by arm and leg strength and power exercises, balance and coordination to prevent falls, flexibility and cardiovascular endurance (i.e walking) exercises [16, 30]. The proposed exercises’ sets and repetitions, intensity of progression of each Program are shown in Table 3 and illustrated in Fig. 2.

**Table 3 Tab3:** Proposed exercises sets, repetitions (Reps) and intensity (Intst) of progression of each program of the VIVIFRAIL© multicomponent exercise methodology

		Program A	Program B		Program C 1 and C2	Program D
**Resistance training**	Sets / Reps	Week 1–2: 2 sets / 10 reps Week 3–4: 2 sets / 10 reps Week 5–6: 2 sets / 10 reps Week 7–8 2 sets / 10 reps Week 9–10: 2 sets / 10 reps Week 11–12: 2 sets / 10 reps	Week 1–2: 2 sets / 10 reps Week 3–4: 2 sets / 12–15 reps Week 5–6: 3 sets / 12 reps Week 7–8 2 sets / 10 reps Week 9–10: 2 sets / 12–15 reps Week 11–12: 3 sets / 12–15 reps			
	Intst	Determine the weight that allows to do the exercise properly without stopping yet makes feel as though they have made an effort by the end: Week 1–6: 30 times Week 6–12: 20 times				

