**Fig. 2 Fig2:**
[figure not shown]
Proposed exercises illustration of each program of the VIVIFRAIL© multicomponent exercise methodology. Modified from Izquierdo and colleagues (2017)

The intervention will be discontinued due to any condition or adverse event that does not allow the performance of exercises with security or if requested by any participant. If necessary, one medical team will be disposable to offer assistance at any moment.

The participants will be instructed to does not enroll in other physical activity intervention during the period of 12 weeks of intervention.

After initial assessment and categorization, the multicomponent program will be carried out for 12 weeks, totaling 60 sessions. Two weekly supervisioned sessions will be held (60 min) with an interval of 1 day between them. Participants will receive all materials (elastic bands, towel and bottles with water/sand) to perform the exercises and will be trained to perform exercises individually at home 3 days weekly in order to complete 5 days per week. Instructions will be adapted to the focused population and will be provided in Portuguese. Adherence to the intervention will be monitored using a frequency control spreadsheet before the start of each session. Participants will be instructed to report possible adverse events.

Participants may withdraw from the study for any reason at any time. The investigator also may withdraw participants from the study in order to protect their safety and/or if they are unwilling or unable to comply with required study procedures. To promote participant retention and complete follow-up, all the participants will receive written feedback regarding the assessments performed.

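### The protocol concedes that the intervention cannot be hidden from participants, then says they will not know their group; participants are not blinded, and at least three secondary outcomes are reported by them

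*Protocol article*

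**What the plan says.** Under *Randomization and blinding*, the protocol article first concedes the point for participants: "It will not be possible to hide the intervention of the participants, who will know about the allocation in different groups at random". The next sentence takes the concession back: "However, they will not be aware of which group they were allocated". The same section says that the professional delivering the intervention cannot be blinded. It also says that the follow-up researcher and the staff doing physical and blood assessments will not know the allocation, and adds: "Raters and data-analysts will keep blinded in relation to the intervention performed by the volunteer".

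The arms are described under *Interventions*. For exercise: "Two weekly supervision sessions will be held, lasting 60 min each, with an interval of 1 day between them", together with home sessions on three further days a week using supplied materials. For control: "participants allocated to control group will participate in monthly meetings of health promotion", with lectures and social activities.

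Fatigue is a secondary outcome based on specific CES-D items. Where those items are described, under *Recruitment and inclusion criteria*, the text reads: "it will be evaluated through self-report using questions 7 and 20". *Secondary measures* describes the Geriatric Depression Scale as 15 questions about how the person felt in the past week, and quality of life as the EQ-5D questionnaire.

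**The concern.** The two sentences cannot both describe this trial. A person who attends supervised exercise twice a week and trains at home with elastic bands knows that they are in the exercise group. A person invited to a monthly lecture knows that they are not.

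What is at stake is how the secondary results can be read. When an outcome is the participant's own answer, the participant is in effect the assessor, and keeping the rater unaware does not remove the influence of knowing one's group. A hopeful exercise participant may report less fatigue or better mood whatever the physiological effect, and a disappointed control may do the reverse. *Secondary outcomes* hypothesises improvement on exactly these measures. If the sentence on participant unawareness stays, a reader of the results could take the trial to have a protection that it does not have.

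**Working it through.** No sample size, power or error rate is involved. The check compares the sections with one another and adds a short count of scheduled contacts.

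**1. Blinding, party by party** (*Randomization and blinding*)

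| Party | What the protocol says | Consistent with the design? |
|---|---|---|
| Participants | Intervention cannot be hidden, yet group unknown to them | No |
| Intervention professional | Not blinded | Yes |
| Physical and blood assessors, follow-up researcher | Blinded | Nothing in the text contradicts it |
| Raters and data analysts | Blinded | Nothing in the text contradicts it |

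**2. Could participants be unaware?** This would need arms that look alike or some concealment. The article describes no sham exercise, no attention-matched activity and no withholding of which arm is experimental. Participants are also told that there are different groups assigned at random.

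**3. When does knowledge begin?** The envelopes are delivered after baseline measurement, so baseline answers precede allocation. The answers at weeks 12 and 24 do not, and change from baseline inherits the problem.

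**4. Which outcomes are exposed?** Taking only what the text establishes:

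- Fatigue: stated to be self-report.
- Geriatric Depression Scale: questions on how the participant felt.
- EQ-5D: a questionnaire on the participant's own health state.
- FRAIL-BR and SARC-F: the article does not say how they are completed, so they are not counted.

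That gives at least three secondary outcomes. The primary outcome (*Primary outcomes*, *Inflammation*) is measured by ELISA in serum and culture supernatants, so it is not open to reporting bias.

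**5. Scheduled contact over the 12 weeks**

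- Exercise, supervised: 2 per week × 12 weeks = 24 sessions.
- Exercise, at home: 3 per week × 12 weeks = 36 sessions.
- Total: 24 + 36 = 60, which reproduces the protocol's stated 60 sessions.
- Control: one meeting a month, taking a month as about 4 weeks, gives 12 / 4 = about 3 meetings. The article does not state this count.

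The arms therefore differ in scheduled supervised contact, 24 against about 3, as well as in content.

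**The case against.** The strongest reply is that the sentence is awkward English. On this reading, participants know what they are doing but not which arm is the experimental one. The protocol does admit that the intervention cannot be hidden, and its explicit blinding claims concern assessors, raters and analysts. That reading is possible, but the sentence speaks of the group to which they were allocated, and no step is described that would keep the experimental arm unknown to them. The text needs correcting on either reading.

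Other parts of the objection do stand and limit the point:

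- A reader might infer that the protocol presents its self-reported outcomes as blinded. It nowhere says so. The defect is a false statement about participants, from which such a belief could follow.
- A reader might count most of the secondary outcomes as self-reported. The article supports three; the mode of completion of FRAIL-BR and SARC-F is not given.
- A reader might call all the remaining performance tests effort-dependent. Gait for the frailty criteria is measured at the person's usual pace, and grip follows a fixed procedure with familiarisation and three trials. Follow-up assessors are also unaware of allocation.
- A reader might conclude that the control meetings fail in their stated purpose. The *Control group* section aims to reduce the effect of socialization; it does not promise equal contact. The length of the meetings is not given and telephone calls follow absences, so 24 against about 3 counts scheduled encounters and does not measure attention.

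**Conclusion.** The contradiction is real, and the statement that participants will not know their group is wrong for this design. It should be corrected. Its reach is limited: the laboratory primary outcome is not exposed to reporting bias, and the sample size and primary analysis do not change. At least three secondary outcomes with hypothesised benefit (fatigue, Geriatric Depression Scale, EQ-5D) are reported at weeks 12 and 24 by people who know their assignment, and with more supervised contact scheduled in one arm.

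The documents give no basis for estimating the size of any resulting bias, and none is claimed here. The conclusion assumes that no concealment procedure exists beyond what the article describes, and that monthly means about one meeting every four weeks.

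**What to change.** In *Randomization and blinding*:

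1. Delete the sentence saying that participants will be unaware of their group.
2. State that participants and the professionals delivering the intervention are not blinded, and that blinding covers outcome assessors, laboratory staff and data analysts only.
3. Add that participants will be asked not to disclose their group to assessors at weeks 12 and 24. This protects the blinding that the trial does have.

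In *Secondary outcomes* or the analysis section, state that the participant-reported outcomes are unblinded, that more supervised contact is scheduled in the exercise arm, and that these results will be interpreted with that limitation.

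Recording each assessor's guess of allocation at the two follow-up visits is optional. It would show whether assessor blinding held, for one extra item on the form.

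The cost is a few lines of protocol text and one instruction to participants at visits already planned. The real price is a weaker claim for the participant-reported outcomes, which the design imposes in any case.

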### Measurements

Outcome measures will be done at three moments: baseline, after 12 weeks (end of intervention), and 24 weeks.

#### Inflammation

The peripheral blood of all participants will be collected. From everyone, approximately 9 mL of blood will be collected in tubes containing clot activator and 9 mL in tubes containing sodium heparin for peripheral blood mononuclear cells (PBMCs) and polymorphonuclear cells (PMNs) isolation. The serum will be separated after clot formation by centrifugation at 1200 *g* for 15 min at room temperature, then the serum will be collected, aliquoted and immediately stored at 20 °C. The cytokine measurement will be performed using ELISA with specific commercial kits for IL-6, TNF- α, IL1beta, IL-17, IL-22, CXCL-8, IL1RA, and IL-27 (R&D Systems and Biolegend manufacturers’ instructions).

PBMCs will be isolated using Ficoll-Hypaque density gradient centrifugation (density 1.077 - Pharmacia Biotech, Piscataway, NJ, USA). After removing PBMCs, the buff-coat cells (containing PMNs) will be collected and diluted in fresh RPMI medium and submitted to new centrifugation over a Ficoll-Hypaque solution at a density of 1.119). After separation, PBMCs and PMNs will be resuspended (2 × 10^6^ cells/mL) in RPMI medium supplemented with fetal bovine serum (10%), L-glutamine, sodium pyruvate and gentamicin (RPMI-S) and distributed in 24-well plates. Cultures will be maintained without additional stimulation or stimulated with ultrapure LPS (100 ng/mL - Invivogen) and PMA (100 ng/mL - Sigma) for PMNs and with ultrapure LPS (100 ng/mL - Invivogen) and PHA (10 mg/mL) for PBMCs. The cells will be kept for 24 h, at 37 °C in a CO_2_ incubator (5%). After the culture period, the supernatant will be collected and stored at − 80 °C and will be evaluated by ELISA with commercial kits for each cytokine (IL-10, IL-4, IFN-gamma, IL-17, TNF- α, IL-6) (R&D Systems and Biolegend).

The details of the pro-inflammatory and anti-inflammatory mediators investigated in this study are presented in the Table 2.

**Table 2 Tab2:** Pro-inflammatory and anti-inflammatory mediators

Mediator	Major Cellular Sources	Major Activities
**IFN-gamma**	Th1 cells, NK cells	Activation of inflammatory macrophages (M1), inhibition of Th2 responses, induction of leukocyte migration.
**IL-1beta**	Monocyte/macrophages, PMNs.	Synthesis of acute-phase proteins by hepatocytes, induction of local and systemic inflammatory effects.
**IL-1RA**	Monocyte/macrophages, dendritic cells.	Specific inhibitor of IL-1alpha and IL-1beta by competition with the cellular receptor.
**IL-4**	Th2 cells, mast cells, B cells	Induction of Th2 lymphocyte development, inhibition of pro-inflammatory and Th1 cytokine production, activation of anti-inflammatory macrophages (M2).
**IL-6**	Monocyte/macrophages, T cells, PMNs.	Produced during the inflammatory response, induces the synthesis of acute-phase proteins by hepatocytes, but presents an inhibitory effect on TNF- α and IL-1 production by macrophages.
**IL-8 (CXCL8)**	Monocytes/macrophages, PMNs.	Major chemotactic cytokine (chemokine) for neutrophils.
**IL-10**	Monocyte/macrophage, Th2 cells, B cells	Inhibition of pro-inflammatory cytokine production by macrophages and neutrophils, inhibition of Th1 cytokine production.
**IL-17**	Th17 cells	Activation of neutrophils, induction of extracellular matrix remodeling.
**IL-22**	Th17 and Th22 cells	Induction of epithelial cell proliferation and production of antimicrobial peptides by epithelial cells and neutrophils.
**IL-27**	Macrophages, dendritic cells.	Antagonist of Th1, Th2 and Th17 inflammatory responses, induction of Tr1 (regulatory) cells.
**TNF-** α	Monocyte/macrophages, PMNs, T cells.	Synthesis of acute-phase proteins by hepatocytes, recruitment, and activation of cells into inflammatory sites, induction of insulin resistance.

#### Physical performance

The SPPB battery allows the evaluation of the performance of the lower limbs. It is composed of the assessment of standing balance, gait speed and muscle strength. The SPPB varies between 0 and 12 points, with higher score representing better performance. It is a valid instrument for screening for frailty and predicts disability, institutionalization and death, so that a change of 1 point represents a relevant issue [23, 24].

#### Secondary measures

The gait evaluation during the simultaneous performance of a cognitive task is a useful tool for functional evaluation in frail older patients, allowing to predict falls [25]. The participants will perform a 6 m gait velocity test (6 m-GVT) while naming animals aloud. The cognitive score during the dual task will be measured by counting the number of animals named. Depression symptoms will be evaluated throughout the Geriatric Depressive Scale (GDS) [26], composed by 15 items in which mental health related questions are asked in reference to how the participants felt over the past week. The quality of life will be evaluated though the EQ-5D questionnaire (“EuroQol - a new facility for the measurement of health-related quality of life,” 1990). The questionnaire its composed by five dimensions (mobility, self-care, usual activities, pain/discomfort and anxiety/depression with 3 levels (no problems, some problems, and extreme problems). All participants also will be assessed with FRAIL-BR [1] and SARC-F [27, 28].

To register the physical activity frequency after the intervention period, a diary will be used and the times per week of physical activity performed by the participants will be computed.

### Interventions

#### Control group

To ensure that possible changes in the serum levels of biomarkers were not related to frailty, participants allocated to control group will participate in monthly meetings of health promotion. To minimize bias effect of socialization on the perception of health, the meetings will include lectures on topics related to health, such as food, use of medicines, prevention and health promotion and socialization activities [29]. Participants will be guided to continue the usual primary and secondary health care (public or private) and community activities. Telephone contact will be made after absences from meetings.

#### Intervention group

The VIVIFRAIL© [15, 19] multicomponent exercise intervention protocol was developed in Europe (Erasmus+programme, European Union) and consists of resistance training, gait retraining, and balance training. Different functional capacity levels will be determined based on the scores obtained from the SPPB and the 6-m gait velocity test, with each leading to the recommendation of a certain customized multicomponent physical exercise program (Program A, B, C1, C2 or D). These programs are composed by arm and leg strength and power exercises, balance and coordination to prevent falls, flexibility and cardiovascular endurance exercises [15, 19].

After the initial assessment and categorization of the volunteer in any of the physical exercise programs, a multicomponent program will be carried out for 12 weeks, totaling 60 sessions. Two weekly supervision sessions will be held, lasting 60 min each, with an interval of 1 day between them. Participants will receive the materials (elastic bands, towel and bottles with water/sandy) to perform the exercises and will be trained to perform exercises individually at home with a frequency of 3 days a week, in order to complete 5 days of activity per week. Instructions will be properly adapted to the focused population and will be provided to the volunteers in the Portuguese language.

The VIVIFRAIL© program is composed by arm and leg strength and power exercises, balance and coordination to prevent falls, flexibility and cardiovascular endurance (i.e walking) exercises [16, 30]. The proposed exercises’ sets and repetitions, intensity of progression of each Program are shown in Table 3 and illustrated in Fig. 2.

**Table 3 Tab3:** Proposed exercises sets, repetitions (Reps) and intensity (Intst) of progression of each program of the VIVIFRAIL© multicomponent exercise methodology

		Program A	Program B		Program C 1 and C2	Program D
**Resistance training**	Sets / Reps	Week 1–2: 2 sets / 10 reps Week 3–4: 2 sets / 10 reps Week 5–6: 2 sets / 10 reps Week 7–8 2 sets / 10 reps Week 9–10: 2 sets / 10 reps Week 11–12: 2 sets / 10 reps	Week 1–2: 2 sets / 10 reps Week 3–4: 2 sets / 12–15 reps Week 5–6: 3 sets / 12 reps Week 7–8 2 sets / 10 reps Week 9–10: 2 sets / 12–15 reps Week 11–12: 3 sets / 12–15 reps			
	Intst	Determine the weight that allows to do the exercise properly without stopping yet makes feel as though they have made an effort by the end: Week 1–6: 30 times Week 6–12: 20 times				
**Cardiovascular training**	Sets / Reps	Time walking / rest / times Week 1–4: 5–10s / 10s / 5–7 Week 5–6: 10–15 s / 20s / 5–7 Week 7–8: 15–30s /20s / 5–10 Week 9–10: 30–45 s / 20s / 5–10 Week 11–12: 45–60s /20s/12–15	Time walking / rest / times Week 1–4: 20s / 10s / 5–7 Week 5–6: 20–25 s / 20s / 5–7 Week 7–8: 25–35 s /20s / 5 Week 9–10: 45 s / 20s / 5 Week 11–12: 50–70s /20s/12–15	Time walking / rest / times		Time walking / rest / times Week 1–2: 15 min / 30s / 2 Week 3–4: 15 min / 30s / 3 Week 5–6: 20 min / 30s / 2 + 15 min Week 7–8: 30-35 min /30s / 2 Week 9–10: 50–70 min Week 11–12: 50–70 min
				C1	Week 1–2: 3-5 min / 30s / 2 Week 3–4: 5 min / 30s / 2 Week 5–6: 5 min / 30s / 3 Week 7–8: 5-7 min /30s / 3 Week 9–10: 7–12 min Week 11–12: 12–20 min	
				C2	Week 1–2: 8-10 min / 30s / 2 Week 3–4: 10 min / 30s / 2 Week 5–6: 5-10 min / 30s / 3 Week 7–8: 15-25 min Week 9–10: 25–30 min Week 11–12: 30–40 min	
	Intst	Usual walking pace				
**Balance training**	Sets / Reps	Remain in the same position, and do 2–3 times with each leg, counting to: Week 1–2: 5–10 Week 3–4: 10 Week 5–6: 15 Week 7–8: 20 Week 9–10: 25 Week 11–12: 30	Remain in the same position and do 2–3 times with each leg, counting to: Week 1–2: 10 Week 3–4: 15 Week 5–6: 20 Week 7–12: 30 + Walk 10 steps/ 2 times + Walk in a relaxed way and step over 5 obstacles / 8 times	Remain in the same position counting to: Week 1–2: 10 Week 3–4: 15 Week 5–6: 20 Week 7–12: 30 These exercises will be done 2 times with each leg, followed by: Walk 10 steps/ 2 times + Walk in a relaxed way and step over 5 obstacles / 8 times		
**Flexibility**	Intst	-Change the position of the arms; -Cross your arms - Use of different surfaces - Eyes closed.				
	Sets / Reps	Week 1–6: 2 sets of 3 reps Week 7–12: 3 sets of 3 reps				
	Intst	Remain in the same position for 10–12 s

